#### Cost analysis

The Trimbos/iMTA questionnaire for Costs associated with Psychiatric Illness
(Tic-P) will be used to measure treatment costs and additional expenses
[67]. The subsection on
absence from work (productivity loss by absenteeism and by loss of
productivity while at work, and informal care and domestic help) is filled
in every month. The subsection on health care costs (medical treatments,
paramedic therapy, alternative therapy, self-care groups, clinical or
outpatient treatment in hospital and other institutions, and medication) is
filled in every 3 months. Treatment hours are registered by the therapists
and the rehabilitation physicians in checklists filled in after each
treatment session. The valuation of health-care costs, patient and family
costs will be based on the updated Dutch manual for cost analysis in
health-care research [68]. For care
for which no costs-guidelines are available, estimations of the costs will
be made based on the real costs or on population-based estimates from the
literature.

### Assessment and procedures

After inclusion, the research assistant contacts the patient to make an
appointment for the baseline assessment (T1). During T1 the patient is asked to
wear the activity monitor for one week and to fill in the following
questionnaires: 

 Checklist Individual Strength (CIS)

 Short Form 36 (SF-36)

 EuroQol- 5D (EQ-5D)

 Symptom Check List-90 (SCL-90)

 Self-Efficacy Scale-28 (SES 28)

 Causal Attribution List (CAL)

 Mindfulness Attention Awareness Scale (MAAS)

 Sickness Impact Profile-8 (SIP-8)

 Life Satisfaction Questionnaire, Dutch Version (LSQ-DV)

The patient is instructed on how to fill in the Tic-P, part II on health- and
non-health-related costs every month for 1 year. One week after baseline
assessment, the research assistant collects the activity monitor. The research
assistant gives the patient a blind envelope with the treatment conditions.
Treatments start within 4 weeks. Two weeks after the start of treatment, a
patient is asked to fill in the list of Borkovec and Devilly and the PSCG, part
1. At 3 and 9 months after T1 a patient is asked to fill in the Tic-P, part I at
home. Six months after the start of treatment the research assistant assesses
the patient again (T4). The patient is asked to wear the activity monitor and
fill in the same questionnaires as in T1 completed by the PSCG, part II
self-rated improvement questionnaire and Tic-P, part I. Twelve months after the
start of the treatment, the same assessment as in T4 will be repeated (T5). For
each patient the study takes 12 months.

### Randomisation

After signing the informed consent form the patients are randomly divided into
two groups: CBT and MRT. For each rehabilitation centre a randomisation list was
generated by computer under supervision of an independent statistician. Before
recruitment of patients an independent person prepared sealed envelopes for each
rehabilitation centre and numbered them sequentially according to the
randomisation list. The envelope is given to the participating patient by an
independent research assistant after baseline assessment. The patient is asked
not to open the envelope in front of the research assistant. Randomisation is
performed for each centre to prevent differences between the treatment groups in
the distribution of centres.

### Adverse events

Patients are able to contact a physician, who is appointed as an independent
physician for the study, at any time. Adverse events will be monitored
carefully. If any adverse event occurs or a patient withdraws from treatment,
the researcher or research assistant will ask the patient and the therapist(s)
why the patient is withdrawing. If deterioration is reported, the patient is
offered appropriate help if needed. Referrals to other institutions are
registered. Each patient withdrawing from treatment is asked to participate in
the follow-up measurements. Patients who are not willing to participate in the
follow-up measurements are asked to fill in questionnaires at home without
wearing the activity monitor. Reasons for not wanting to participate in the
follow-up measurement are registered.

### Analyses

#### Sample size

Based on the available literature [25,34,69] and our pilot
study, mean CIS-fatigue scores at the start of CBT or multidisciplinary
rehabilitation are about 50–52 with a standard deviation of 3.9-5.9.
Following previous trials [28,34], we assume that a difference of 0.5 SD of the
mean group score at baseline is clinically relevant. This equals a
difference of about 3.0 points on the CIS fatigue scale. With a sample size
of 48 patients in each treatment arm, accepting an alpha error of 0.05 and a
power of 0.80, it is possible to measure a minimal difference of 3.0 points
on the CIS fatigue scale. To compensate for an estimated 25% dropout rate, a
total of 120 people will be included.

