### Hypotheses on the primary objectives

 (1) MRT is more effective than CBT in reducing fatigue severity and increasing
quality of life 6 months after start of treatment.

 (2) MRT is more effective than CBT in reducing fatigue severity and increasing
quality of life 12 months after start of treatment.

 (3) MRT is more cost-effective than CBT when data on medical and non-medical
costs are compared over a 12-month period and shows a higher cost-utility.

 (4) MRT is more effective than CBT in increasing self-efficacy, non-physical
attributions, present-centred attention-awareness and life satisfaction, and is
more effective in decreasing the impact of disease on physical and emotional
functioning and decreasing the psychological symptoms. Self-rated improvement is
significantly higher in MRT than in CBT (at 6- and 12-month follow-up).

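### The 80% power claimed for 48 patients per arm fits the stated effect and SD only under an undeclared one-sided 0.05 test; an unadjusted two-sided test has about 68-70%

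*Protocol article*

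**What the plan says.** The Sample size section of the protocol article gives baseline CIS-fatigue means of about 50-52 "with a standard deviation of 3.9-5.9". On the clinically relevant difference it says "we assume that a difference of 0.5 SD of the" baseline group score matters, and converts this into a "difference of about 3.0 points on the CIS fatigue scale". The power statement rests on "48 patients in each treatment arm, accepting an alpha error of 0.05". For that number of patients it claims 80% power to detect a 3.0-point difference. The section does not say whether alpha is one- or two-sided, which SD in the range was used, or whether any gain from baseline adjustment was counted.

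Three other places bear on the reading:

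- **Hypotheses on the primary objectives** is directional for fatigue and for quality of life alike ("MRT is more effective than CBT in reducing fatigue severity and increasing", and so on).
- **Aims of the study** is neutral. It speaks of assessing differences between the two treatments, and the end of the Relevance section asks which of them is the most effective.
- **Analyses of efficacy** plans a mixed linear regression with the baseline value as covariate. It names no sidedness.

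**The concern.** A target of 0.5 SD fixes the standardised effect, so the sample size for an unadjusted two-group comparison follows from alpha, sidedness and power alone. At two-sided 0.05 and 80% power that number is well above 48. An unqualified alpha of 0.05 is normally read as two-sided, so most readers will take the trial to have 80% power for its own clinically relevant difference under a two-sided test.

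The Trial status section says that data collection is complete and analysis is to follow, so the sample size can no longer change. What is still open is how a non-significant comparison of multidisciplinary rehabilitation treatment (MRT) with cognitive behavioural therapy (CBT) may be read. A trial with 80% power misses a true 0.5 SD benefit one time in five; a trial with 68-69% power misses it nearly one time in three. If a one-sided 0.05 test was intended, readers need to know that too, because it allows a 5% error rate in MRT's favour where a two-sided 0.05 test allows 2.5%.

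**Working it through.** **Inputs (all from the Sample size section).** Difference δ = 3.0 points; δ = 0.5 SD; SD range 3.9-5.9; α = 0.05; power 0.80; n = 48 per arm, taken as the number analysed.

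**Step 1. Which SD is implied?** Half of 3.9 is 1.95 and half of 5.9 is 2.95. Only the top of the range gives about 3.0 points, and exactly 3.0 would need SD 6.0. So SD is about 5.9-6.0.

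**Step 2. Reproduce the stated 48.** Normal approximation: n per arm = 2 × SD² × (z_α + z_β)² / δ², with z_β = 0.842.

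- One-sided 0.05 (z = 1.645), SD 5.9: 2 × 34.81 × 6.183 / 9 = 47.8, so 48. Power at 48 is 0.801.
- One-sided 0.05, SD 6.0: 2 × 36 × 6.183 / 9 = 49.5, so 50. Power at 48 is 0.790.
- Two-sided 0.05 (z = 1.960), SD 5.9: 2 × 34.81 × 7.849 / 9 = 60.7, so 61.
- Two-sided 0.05, SD 6.0: 2 × 36 × 7.849 / 9 = 62.8, so 63.

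The plan's figure is therefore reproduced exactly by a one-sided 0.05 test at SD 5.9. No two-sided unadjusted calculation at SD 5.9-6.0 gives it.

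**Step 3. Two-sided, unadjusted power with 48 per arm.** Normal approximation: power = Φ(δ / (SD × √(2/48)) − 1.960). The t column uses the noncentral t distribution.

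| SD | δ/SD | Power, normal | Power, t | n per arm for 80%, t |
|---|---|---|---|---|
| 5.9 | 0.508 | Φ(2.491 − 1.960) = 0.702 | 0.693 | 61.7, so 62 |
| 6.0 | 0.500 | Φ(2.449 − 1.960) = 0.688 | 0.679 | 63.8, so 64 |

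By the t calculation, type II error is 0.307 to 0.321 against the stated 0.20.

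**Step 4. Difference detectable with 80% power, two-sided, 48 per arm.** The noncentral t gives 0.578 SD: 0.578 × 5.9 = 3.41 points and 0.578 × 6.0 = 3.47 points.

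**Step 5. What baseline adjustment could add.** Adjusting for baseline multiplies the SD by √(1 − ρ²), where ρ is the baseline/follow-up correlation. The article gives no ρ, so the values below are assumptions. Two-sided 0.05, 48 per arm, 0.5 SD, noncentral t:

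| Assumed ρ | √(1 − ρ²) | Power |
|---|---|---|
| 0.3 | 0.954 | 0.72 |
| 0.5 | 0.866 | 0.80 |
| 0.6 | 0.800 | 0.86 |

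These figures also assume that the spread at follow-up equals the spread at baseline.

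**Step 6. Another two-sided route to 48.** At SD 5.2, 3.0 points needs 47.2 per arm by the normal approximation, so 48 (48.1 by t). But 3.0 / 5.2 = 0.58 SD, which is not the 0.5 SD that the section sets.

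**The case against.** The strongest reply is that nothing here is shown to be a miscalculation. Sidedness is never stated, the hypotheses are directional, and 48 reproduces exactly under a one-sided reading that the text does not exclude. That stands, and a reader who infers that the true power of the trial is 68-69% goes further than the document allows. Directional hypotheses do not settle the matter, however: they state what the investigators expect, while the aims ask neutrally which treatment is better.

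Second, the planned analysis adjusts for baseline, so an unadjusted calculation may understate its power. This also stands, but only conditionally. It takes a correlation of about 0.5 to reach 80%, and the sample size section works from a baseline SD without mentioning any correlation. Entry requires CIS-fatigue of 40 or more on a scale that ends at 56. That restricts the spread at baseline, so an equal spread at follow-up cannot be taken for granted.

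Third, the power sentence is in points and the SD range runs down to 3.9. For 3.0 points, two-sided unadjusted power at 48 per arm is 0.96 at SD 3.9, 0.84 at 4.9 and 0.80 at 5.2. That is correct, but at those SDs 3.0 points is more than 0.5 SD (0.77, 0.61 and 0.58), which conflicts with the section's own conversion.

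One might also infer a two-sided test from the 95% intervals in the Economic analyses section. Those intervals concern costs only and say nothing about the CIS-fatigue test.

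**Conclusion.** The point holds in a conditional form. At the stated 0.5 SD, taken as about 3.0 points, the combination of 48 per arm, alpha 0.05 and 80% power is consistent only with a one-sided test that is declared nowhere, or with a gain from baseline adjustment that the section does not invoke. For an unadjusted two-sided 0.05 comparison, power is about 68-70%, the requirement for 80% is about 62-64 per arm, and the difference detectable with 80% power is about 3.4-3.5 points. These figures rest on an SD of 5.9-6.0, equal arms and 48 analysed per arm. The documents do not establish that the planned adjusted analysis falls short of 80%, nor that it reaches it; with assumed correlations of 0.3 to 0.6, its two-sided power would lie between 0.72 and 0.86. The power statement should be corrected before results are interpreted, because it governs how a null result can be read.

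**What to change.** Restate the Sample size paragraph so that it names the sidedness of the test, the SD used, and any baseline/follow-up correlation relied on with its source.

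- **If the test is two-sided and unadjusted:** report about 69% power for 3.0 points at SD 5.9, or equivalently 80% power for about 3.4 points (0.58 SD).
- **If baseline adjustment was relied on:** give the assumed correlation and follow-up SD, and the power that results.
- **If a one-sided 0.05 test was intended:** say so in both Sample size and Analyses of efficacy.

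The cost is wording only. No patients are added and the design and analysis model stay as they are. Under the two-sided unadjusted reading, the reported power becomes less favourable.

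### The planned 120 patients do not compensate for 25% dropout: they leave 45 per arm, not the required 48, a small shortfall of about 2 to 3 points of power

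*Protocol article*

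**What the plan says.** The Sample size section of the protocol article sets the requirement at 48 patients per arm with alpha 0.05. It describes what this number buys as follows: "power of 0.80, it is possible to measure a minimal difference of 3.0 points", meaning points of CIS fatigue. It takes half a standard deviation as clinically relevant, which it equates to a "difference of about 3.0 points on the CIS fatigue scale", and it cites earlier data "with a standard deviation of 3.9-5.9".

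The allowance for loss opens with "To compensate for an estimated 25% dropout rate, a" and closes with the figure itself: "total of 120 people will be included". The Methods part of the Abstract repeats the total of 120. The article gives no other dropout rate and no other basis for 120.

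**The concern.** A dropout rate is a fraction of the patients who enter the trial. If a quarter of 120 are lost, the number left is below the 48 per arm that the same paragraph requires, so the stated compensation is not achieved. The error makes the plan look slightly better protected than it is.

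At stake is the accuracy of the stated operating characteristics for the fatigue outcome: how much loss the sample can absorb before power for 3.0 points falls below the stated 0.80. The planned analysis itself is not affected.

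**Working it through.** **Inputs, all from the Sample size section:** 48 per arm (96 in total); difference 3.0 points; SD 3.9 to 5.9; alpha 0.05; power 0.80; dropout 25%; total included 120. The section does not state whether the test is one- or two-sided. The hypotheses on the primary objectives are directional ("MRT is more effective than CBT in reducing fatigue severity and increasing" quality of life).

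**Step 1: reproduce 48 per arm.** Normal approximation, n per arm = 2 x (SD/3.0)^2 x (z_alpha + z_power)^2.
- One-sided, SD 5.9: 2 x (5.9/3.0)^2 x (1.645 + 0.842)^2 = 47.8, rounded up to 48.
- Two-sided, SD 5.2: 2 x (5.2/3.0)^2 x (1.960 + 0.842)^2 = 47.2, rounded up to 48.
- Two-sided, SD 5.9: 60.7, rounded up to 61, so this setting does not reproduce 48.

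Two sets of assumptions therefore lead to 48. The dropout check does not need to choose between them, because it starts from 48.

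**Step 2: reproduce 120.**
- Multiplying by one plus the rate: 96 x 1.25 = 120, an exact match.
- Dividing by the retained fraction: 96 / (1 - 0.25) = 96 / 0.75 = 128, or 64 per arm.

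Only the first formula gives the stated figure. That it was the one used is an inference from the match.

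**Step 3: what 120 delivers.**
- At 25% dropout: 120 x 0.75 = 90, or 45 per arm. Shortfall: 96 - 90 = 6 evaluable patients, or 128 - 120 = 8 randomised.
- Dropout at which 96 remain: 1 - 96/120 = 0.20.

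**Step 4: the cost in power.** Two-sample t-test, 3.0 points, alpha 0.05:

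| Setting | 48 per arm | 45 per arm | Loss |
|---|---|---|---|
| One-sided, SD 5.9 (reproduces 48) | 0.796 | 0.773 | 0.023 |
| Two-sided, SD 5.2 (reproduces 48) | 0.799 | 0.772 | 0.027 |
| Two-sided, SD 5.9 | 0.693 | 0.665 | 0.028 |
| Two-sided, exactly 0.5 SD (SD 6.0) | 0.679 | 0.650 | 0.029 |

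**Step 5: the cost in detectable difference.** At 80% power, two-sided, the t-test detects 0.578 SD with 48 per arm and 0.597 SD with 45. The increase is 0.019 SD, or 0.019 x 5.9 = about 0.1 point at the largest SD quoted.

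**The case against.** The best defence is that dropout need not mean loss from the analysis. The article uses the word both for stopping treatment and for missing a measurement (Analyses of efficacy). Patients who withdraw from treatment are asked to stay in follow-up, or failing that to complete questionnaires at home (Adverse events). The efficacy analysis is by intention to treat, in a mixed model with the baseline value as covariate, which can gain precision. As an illustration only, since the article gives no correlation: with a single follow-up, a baseline-to-follow-up correlation of 0.25 would offset 45 against 48 per arm, because 1 - 0.25^2 = 0.9375 = 45/48. It follows that the power actually attained cannot be said to fall short. The sentence itself is not rescued, because the article offers none of this as the reason for 120 and justifies the figure solely as compensation for 25% dropout.

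One could also read 25% as the size of the uplift. The text calls it a dropout rate, and a 25% uplift covers only a 20% dropout rate.

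In the other direction, a reader might infer from the two-sided figures at 45 per arm (power 0.665 or 0.650, detectable difference 3.5 points at SD 5.9) that the dropout allowance leaves the trial seriously underpowered. The article's figures do not support that. With 48 per arm and no shortfall, the same settings already give 0.693, 0.679 and 3.4 points. Most of the gap to 0.80 comes from the SD and the unstated sidedness, which is a separate question. Nor is power below 0.80 across the whole quoted SD range: at SD 3.9, two-sided power with 45 per arm is 0.950. The lower end sits poorly, however, with the article's own equation of 3.0 points with half an SD.

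**Conclusion.** Wrong as written; minor severity. On the article's own figures, 120 included patients cover 20% dropout, not 25%. The shortfall at 25% is 3 evaluable patients per arm. It costs about 2 to 3 percentage points of power under the assumptions that reproduce 48 per arm, and about 0.02 SD in the two-sided detectable difference.

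The counts rest only on the stated 48 per arm, 25% and 120; sidedness, SD and covariate adjustment do not change them. The power figures assume an unadjusted t-test on the patients who remain, with every dropout lost to the analysis, so they describe the design calculation rather than the planned mixed model. A reader might take it as established that the authors multiplied by 1.25. The exact match makes this likely, but the article does not show the step.

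**What to change.** Correct the one sentence, in either of two ways:
- State that 120 randomised with 25% dropout gives 90 evaluable patients, 45 per arm, and quote the power for 3.0 points at 45 per arm, naming the SD and sidedness used (for example 0.773 one-sided at SD 5.9, or 0.772 two-sided at SD 5.2).
- Or state that 120 preserves 48 per arm only up to 20% dropout.

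If withdrawn patients are expected to remain in the analysis, or if a gain from baseline adjustment is relied on, that should be said and quantified as the justification for 120.

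No added enrolment is asked for. Inclusion ran to January 2011 and the Trial status section reports data collection complete, so the sample cannot change. The cost is one sentence and a slightly less favourable stated figure.

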#### Analyses of efficacy

The effects of therapy conditions on the various outcomes will be compared
using an ‘intention to treat’ approach. Data will be analysed
with mixed linear regression models. The follow-up measurement will be the
dependent variable, and the baseline value of the particular outcome will be
added as covariate as well as random intercepts for individuals to allow for
dependence within patients and centres [70]. Effect modification will be evaluated by
introducing interactions between therapy condition and the potential
modifiers in the equation. There will be a post-hoc analysis of the
non-response group and the missing values. Dropout patients will be asked
about the reason for stopping treatment or not attending a measurement.
Patient characteristics of the dropouts will be compared to those of the
group that completed each treatment. For the analyses we will use SPSS
statistical software.

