### Training the therapists to deliver the interventions

Four rehabilitation teams deliver the multidisciplinary rehabilitation treatment.
Each team consists of one or two rehabilitation physicians or physician
assistants (under supervision of a rehabilitation physician), one or two
psychologists/behavioural therapists, two social workers, two physical
therapists and two occupational therapists. Six other psychologists/cognitive
behavioural therapists deliver the cognitive behavioural therapy in the four
participating rehabilitation centres. The psychologists of the CBT group are not
involved in the multidisciplinary rehabilitation treatment and meetings with a
supervisor will be organised separately for both groups of psychologists.

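### The efficacy model says patient-level random intercepts allow for dependence within centres, which they cannot do; centre, the stratification factor, should be named as a fixed effect

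*Protocol article*

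**What the plan says.** The section Analyses of efficacy of the protocol article sets out a mixed linear regression. The outcome at follow-up is the dependent variable, and the baseline value of the same outcome is "added as covariate as well as random intercepts for individuals to allow for" "dependence within patients and centres". The only random effect named is at the level of the individual, and the only adjusting covariate named is baseline. The purpose given for the random intercepts covers both patients and centres.

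The section Randomisation describes a separate computer-generated list for each of the four rehabilitation centres. It gives the reason: randomisation is "performed for each centre to prevent differences between the treatment groups in" how centres are distributed. Centre is therefore the stratification factor. No other section of the article puts a centre term into the efficacy model.

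**The concern.** The sentence gives one term two tasks, and the term can do only the first. A patient intercept handles repeated measures on the same person. It says nothing about whether patients treated at the same centre resemble one another.

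If an analyst fits exactly what is written, centre is absent from the model even though the allocation was balanced on it. Between-centre differences are then counted as unexplained variation between patients, and the benefit of stratifying is partly lost. At stake are the precision of the MRT-CBT comparison and the accuracy of its stated error rate. There is also a problem of reproducibility: two analysts could read the sentence differently and fit different models.

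**Working it through.** The article gives no figure for centre effects, so there is none to reproduce on this point. The planned 48 patients per arm (Sample size) serves below only as the size of the simulated trial.

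**Step 1: what the named model implies.** For patient *i* at visit *j*, the text gives

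y_ij = intercept + treatment + baseline + u_i + e_ij,

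with u_i independent between patients.
- Same patient, two visits: covariance = Var(u), so repeated measures are handled.
- Two patients, same centre: covariance = 0, so dependence within centres is not modelled.
- If centres do differ, that variance is absorbed into Var(u), which is the error against which the arms are compared.

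**Step 2: size by formula.** Suppose centre explains a share *c* of the outcome variance and the arms are balanced within centres. The treatment estimate is then free of centre differences, but its standard error (SE) is calculated as if it were not:

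SE(without centre) / SE(with centre) = 1/√(1 − c)

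- c = 0.01: 1/√0.99 = 1.005, or 0.5% too wide
- c = 0.05: 1/√0.95 = 1.026, or 2.6% too wide
- c = 0.10: 1/√0.90 = 1.054, or 5.4% too wide

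**Step 3: check by simulation.** Inputs from the article: four centres, 48 per arm (so 4 × 24 = 96 patients), two follow-up visits, SD 5.9 (the upper end of the stated 3.9-5.9) and a difference of 3.0 points. Assumptions: centres of equal size, exact 1:1 allocation within each centre, correlation of 0.6 between visits, correlation of 0.4 between baseline and the patient effect, two-sided alpha of 0.05. There were 4000 runs per setting. Each patient's mean over the two visits was analysed with baseline as covariate, which for balanced data is equivalent to the patient-intercept model. Total variance was held fixed while the centre share varied.

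| Centre share (assumed) | SE without / with centre | Excess | Type I error without / with | Power without / with |
|---|---|---|---|---|
| 0 | 1.013 / 1.013 | 0% | 0.052 / 0.054 | 0.816 / 0.816 |
| 0.01 | 1.012 / 1.007 | 0.5% | 0.050 / 0.052 | 0.821 / 0.822 |
| 0.05 | 1.010 / 0.982 | 2.8% | 0.048 / 0.052 | 0.844 / 0.854 |
| 0.10 | 1.005 / 0.949 | 5.9% | 0.036 / 0.049 | 0.850 / 0.879 |
| 0.20 | 0.997 / 0.884 | 12.8% | 0.027 / 0.048 | 0.866 / 0.922 |

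The simulation error on a type I rate near 0.05 is √(0.05 × 0.95 / 4000) = 0.0034. So 0.048 cannot be told from 0.05, while 0.036 and 0.027 lie clearly below it. At a share of 0.10, the actual SD of the estimate from the model without centre was 0.948. That matches the SE with centre (0.949), not the SE without it (1.005).

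The simulated excess is slightly above the formula because the share is defined against the variance at a single visit. Averaging two visits and adjusting for baseline removes some patient-level variance, so centre makes up more of what remains.

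**The case against.** The best reply is that this is a fault of wording. The sentence names centres as something the model is meant to handle, cites a reference for the method, and may be shorthand for random intercepts at both patient and centre level. The article condenses a fuller plan in which the model may be written out. A reader might infer that the investigators overlooked centre altogether; the text does not support that, because the intent is stated.

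The reply does not remove the point. The article goes beyond silence: it names a term and gives it a function that the term cannot have. If a random centre intercept was meant, its variance would be estimated from only four centres, which is a weak basis. On either reading the sentence needs rewriting.

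Two stronger inferences should be resisted.
- **False positives.** A reader might suppose that unmodelled centre clustering inflates the type I error. Here patients are randomised within centres, so the error goes the other way or is absent.
- **Provider clustering.** The article says that six other psychologists or "behavioural therapists deliver the cognitive behavioural therapy in the four" participating centres, while four teams deliver MRT. A reader might conclude that the standard errors are too narrow because therapist and team effects are ignored. The article never claims to model providers, so nothing is misstated, and such detail is commonly left to an analysis plan. It gives no intraclass correlation and no caseloads. With four teams and four centres, MRT team may coincide with centre. Treatment hours are registered by the therapists "and the rehabilitation physicians in checklists filled in after each" session, but the article does not say that provider identity is kept for analysis.

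**Conclusion.** The point holds as a misdescribed model term with a modest, conservative consequence. Random intercepts for individuals do not allow for dependence within centres, and the stratification factor is not explicitly in the model.

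Taken literally, standard errors are about 2.6-5.4% too wide if centre explains 5-10% of outcome variance. In the simulation at a 10% share, type I error falls to 0.036 and power at 3.0 points is 0.850 instead of 0.879. At a share of 1% or less nothing noticeable changes. The centre share is an assumption throughout.

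The conservative direction rests on allocation being close to balanced within centres, which is the article's stated purpose for the separate lists. If the lists did not enforce that balance, leaving centre out would still cost precision but the test would sit near its nominal level. In neither case does it create false positives, and the point does not threaten the trial's conclusions.

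**What to change.** Rewrite the sentence in Analyses of efficacy so that each term has its own task. Centre enters every efficacy model as a fixed effect, with three indicator variables for the four centres. The patient random intercept is kept, and its stated purpose is limited to the correlation among a patient's repeated measurements. A fixed effect is preferable to a random one here because four centres are too few to estimate a centre variance well.

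The cost is three degrees of freedom. With 96 analysed patients, the patient-level comparison goes from 93 (96 less intercept, treatment and baseline) to 90. If centres do not differ at all, almost nothing is lost: simulated power is 0.816 with or without centre. No new data are needed, since each patient's centre is known from the randomisation list. According to the section Trial status, data collection was complete and the analysis still lay ahead, so the wording could be settled before outcomes were compared by arm.
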